### Data storage and protection

Participants’ identity or other personal information will be kept confidential. Participants will be assigned a unique ID number under which all study information will be stored in a secure file on an encrypted and password-protected computer and laptop at the University of Birmingham (UoB). Physical data (eg, Case Report Forms (CRFs)) will be identifiable only by ID number and stored in a locked filing cabinet at the School of Sport, Exercise and Rehabilitation Sciences at UoB, accessible only by the research team. Participants’ personal data (name, date of birth) and consent forms matching them to their ID number, will be stored securely in a locked filing cabinet, separate from all other data and/or in a password-protected master sheet on an encrypted and password-protected computer and laptop at UoB. All serum samples will be stored in Human Tissue Act compliant facilities at UoB for 3 years then destroyed.

All hard copy data collected on CRF’s will be stored in a linked-anonymised format securely for 10 years then destroyed. All personal data (consent forms, master sheet linking participant IDs to names and contact details) will be stored for 10 years then destroyed. All computerised data will be archived on UoB servers in anonymised form for 10 years in the first instance in accordance with the UoB Code of Practice for Research, and the Data Protection Act (2018).

Following analysis for this specific study, all data will be anonymised and entered into a European ‘PANINI’ open access database that this project is part of and may be analysed in future ethically approved research across the PANINI network. The PANINI shared dataset will be made open access at the conclusion of the funding for the PANINI network including this study in 2020 and stored for at least 10 years as an open access searchable published dataset.

### Patient and public involvement

All authors are strong proponents of PPI and engagement with research and believe the findings of the study will be important to aid the facilitation of improvements in the care of frail older hospital inpatients. Given the feasibility nature of this research, the qualitative element of this study will explore opportunities for PPI in the research design of the future clinical trial. The findings of this study will be disseminated to participants on request, and our PPI groups.

## Ethics and dissemination

### Dissemination

The findings of this study will be disseminated through publication of scientific papers in open access scientific journals, public engagement events, online via social media (Twitter, Instagram) and the PANINI project website,^54 55^ presentation at various conferences, and to study participants on request.

### Safety reporting and monitoring

Adverse events (AEs) and serious adverse events (SAEs) will be monitored and if applicable recorded, by the primary researcher at each testing or exercise session and reported weekly to the principle investigator (PI) and reviewed in the case of AEs. SAEs will be reported immediately to the PI who will complete an SAE form indicating causality and severity. The chief investigator (CI) will then submit this to the sponsor’s research governance office, the Research Ethics Committee and University Hospitals Birmingham (UHB) research governance office, within 24 hours. UHB local policies and Standard Operating Procedures for all safety reporting will also be followed by the research team. SAEs related to pre-existing conditions will not be reported. Actions following an AE or SAE would be as standard, that is, direct referral to their clinical care team, who then may wish to treat the AE or SAE themselves or where appropriate refer the participant to another relevant medical professional, and to recommend that the participant withdraw from the study unless they have been cleared to continue exercise by their attending physician.

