### Interventions

All participants will undergo 10 sessions in total throughout the 2-week intervention in either one of the two interventions. All session will be conducted individually under the guidance of a qualified trainer. A maximum of one session will be performed each day, and sessions will not be performed on any more than a maximum of three consecutive days throughout the duration of the study (table 2).

**Table 2 T2:** Study timeline of all major events during each round of recruitment (SPIRIT schedule)

Week	Seated physical activity in ageing (SPAA) study timeline						
	Monday	Tuesday	Wednesday	Thursday	Friday	Saturday	Sunday
0	Identification + participant information sheet distribution	24 hours consideration period	Recruitment, eligibility screening and baseline assessments	Recruitment, eligibility screening and baseline assessments	Recruitment, eligibility screening and baseline assessments	Recruitment, eligibility screening and baseline assessments	–
1	Training	Rest	Training	Training	Rest	Training	Training
2	Training	Rest	Training	Training	Training	Rest	Training
3	Post-intervention assessment	Post-intervention assessment	Post-intervention assessment	Post-intervention assessment	Post-intervention assessment	Post-intervention assessment	–

SPIRIT, Standard Protocol Items: Recommendations for Interventional Trials.

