#### Exercise intervention 1: specially adapted resistance training intervention

This intervention will be comprised of an intensive (5 days/week), short duration (2 weeks), ~35 min per session, machine-based resistance training intervention. The exercises performed will specifically target the lower limbs through a combination of multijoint strength and power training utilising a leg press and leg extension machine (figure 3).

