#### Post-intervention assessment

Primary and secondary dependent variables will be assessed between 1 and 5 days post-intervention cessation. All assessments will be conducted at least 24 hours post the cessation of the last training session.

Adherence rates in the intervention will be recorded as the number of repetitions completed in a set (100% required for adherence to that exercise), and the number of exercises for which there was 100% adherence. If participants meet these parameters for each exercise session, they will be considered to be in 100% adherence to the intervention. For example, if a participant adheres to 100% of the intervention for nine sessions, but only 90% for one session, then they will have a 99% adherence rate. Adherence rates, whether high, or low, may signify that the interventions may have been too demanding, too easy or optimal. Information will also be collected throughout the study related to uptake and retention rates.

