### Sample size

This study aims to recruit a convenience sample of n =~30 participants: 15 in each intervention. No formal power calculations were conducted due to the feasibility nature of this study. This sample size was based on initial expectations related to the obtainment of data saturation in the qualitative component of the study given its phenomenological approach.^50 51^

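### The exemption of SAEs related to pre-existing conditions has no exception for worsening or possible relation to exercise, and its place relative to the causality assessment is not stated

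*Protocol article*

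**What the plan says.** Everything on harms stands in one section of the protocol article, Safety reporting and monitoring. AEs and SAEs "will be monitored and if applicable recorded, by the primary researcher at each testing or exercise session". For serious events, "SAEs will be reported immediately to the PI who will complete an SAE form indicating causality and severity". The chief investigator then passes the form to the sponsor's governance office, the ethics committee and the hospital governance office within 24 hours. The section adds that "UHB local policies and Standard Operating Procedures for all safety reporting will also be followed by the research team". The next sentence is the exemption: "SAEs related to pre-existing conditions will not be reported".

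The article does not define what makes a condition pre-existing or an event related to it. It does not separate a stable condition from a worsening one, and it does not name who applies the exemption. The exemption covers serious events only and speaks of reporting. It does not say that these events go unrecorded.

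**The concern.** Under Eligibility, every participant must be frail by the Fried phenotype, an inpatient and at least 65 years old. Under Design overview, entry criteria are otherwise kept as few as safety allows. So nobody enters without a pre-existing condition, and the Background itself ties frailty to hospitalisation, disability and death. A fall, a prolonged stay or a death during the study could be attributed to frailty or comorbidity in good faith.

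Being related to an existing condition does not rule out being provoked by exercise, since exercise may be what makes the condition worse. The exemption treats the first as enough to end reporting. What is at stake is independent oversight of current participants and the completeness of the SAE count that the future trial's planners will read.

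**Working it through.** There is no figure in the plan to reproduce. The article gives no SAE rate, and the Sample size section makes no power calculation. The check is mainly a reading of the text.

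**1. Does the flaw depend on where the exemption sits?** The text allows two readings.

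- *Exemption applied before the PI's form.* An SAE labelled pre-existing never reaches the causality assessment, so nobody is asked whether exercise contributed.
- *Exemption applied after the form, as a limit on onward submission.* The PI does judge causality. But the sentence is unqualified, so an event judged related both to an existing condition and possibly to exercise is still exempt.

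On either reading, a possibly exercise-provoked worsening can be kept from the three outside bodies. The order matters for how many such events are examined at all, and the article leaves it open.

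**2. Who falls outside the described route of capture?** Inputs: "All participants will undergo 10 sessions in total throughout the 2-week intervention" (Interventions), the calendar in Table 2, and "Primary and secondary dependent variables will be assessed between 1 and 5 days post-intervention cessation" (Post-intervention assessment).

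- Table 2 has 10 training days and 4 rest days in the 14-day intervention: Tuesday and Friday of week 1, Tuesday and Saturday of week 2.
- Each rest day stands alone and is followed by a training day. The last session is followed by an assessment, which is itself a testing session.
- A participant who continues is therefore seen again, and a rest-day event can be picked up then.
- A participant who stops sessions, transfers or dies has no later session. The section also recommends withdrawal after an AE or SAE unless the attending physician clears further exercise, so the described route can end for people who have already had an event.

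**3. Illustration of how an exemption thins the count.** Input from the document: "This study aims to recruit a convenience sample of n =~30 participants: 15 in each intervention". Assumptions, not from the documents: SAE risk per participant p of 5% to 20%, share of SAEs exempted f of 0% to 90%, at most one SAE per participant, independence between participants.

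Chance that no SAE is escalated among 30 participants = (1 − p(1 − f))^30.

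| Assumed p | Expected SAEs (30p) | f = 0 | f = 50% | f = 75% | f = 90% |
|---|---|---|---|---|---|
| 5% | 1.5 | 21.5% | 46.8% | 68.6% | 86.0% |
| 10% | 3.0 | 4.2% | 21.5% | 46.8% | 74.0% |
| 20% | 6.0 | 0.1% | 4.2% | 21.5% | 54.5% |

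For example, at p = 10% and f = 50%, (1 − 0.05)^30 = 21.5%, against (1 − 0.10)^30 = 4.2% with no exemption. The table shows the direction and how strongly the answer depends on f. Since neither p nor f is known, it does not estimate the effect in this trial.

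**The case against.** The best defence has four parts.

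- **Capture.** A reader might infer that events are captured only at sessions and that rest-day events are lost. The text does not say only. It does not confine recording to events that occur during a session, and hospital procedures for safety reporting also apply. Table 2 brings continuing participants back the day after each rest day. This stands. What is left is the smaller group with no later session, and the hospital procedures, whose content is not shown, may cover them.
- **Contradiction.** A reader might infer that the exemption flatly contradicts the causality step. The sentence comes after the steps for the form, onward submission and hospital procedures, so it can be read as limiting onward submission once the PI has judged. This stands: the order is ambiguous, and no definite contradiction is shown. It does not rescue the rule, because the missing exception for worsening does harm under both readings.
- **Meaning of reported.** In this section the word mainly means notification of the PI, sponsor, ethics committee and hospital. Exempted events could still be recorded and published, and participants are referred to their care team in any case. This stands, so a clean published safety record cannot be inferred. Still, nothing in the article requires these events to be tabulated, and non-escalation is itself a loss of oversight.
- **Article form.** Recording windows, ward-record checks and table layouts are normally left to the full protocol or operating procedures. This stands, and the absence of such detail is not criticised here. The exemption is different: it is a stated rule, and it is too wide as stated.

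**Conclusion.** The point holds as a badly fixed rule. As written, it permits a serious worsening, possibly provoked by the exercise, to be classed as pre-existing and not escalated to the sponsor, the ethics committee and the hospital office. It leaves open whether the PI's causality assessment comes first. SAE counts may be understated, and Design overview provides no control group whose background rate could show it.

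The size is unknown, because the documents give neither an SAE rate nor a breakdown by cause. The conclusion rests on the unqualified wording and on frailty being an entry criterion. It also assumes that the hospital procedures, not shown, do not override the sentence.

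Three further inferences are not supported:

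- The documents do not show that worsening of existing disease is the likeliest harm here.
- They do not say that safety decides whether the future trial goes ahead. It is not among the eight areas of focus, and no go/no-go rule is stated.
- An upper confidence bound for zero events in 30 or 15 participants does not measure this defect. It reflects sample size under complete capture, and the article draws no such inference.

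**What to change.** Reword the safety section along these lines:

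- Every SAE goes to the PI for the causality and severity form before any exemption is considered.
- An SAE is exempt from onward reporting only if it reflects a pre-existing condition that has not worsened in severity or frequency and the PI judges it unrelated to the study procedures.
- All SAEs, exempt or not, are recorded and tabulated by intervention, including those in participants who stop sessions, transfer or die before a later session.

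The cost is a few more SAE forms and a protocol amendment. Under Trial status, the study began on 3 September 2018 with data collection expected to finish on 9 August 2019, so the amendment would come after the start. If data collection has ended, the tabulation can still be attempted from recorded events and ward records. The report should then state which SAEs were exempted and on what grounds.

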Limited-efficacy testing	Is 2 weeks a sufficient duration to potentially provide significant benefit to patients? Can intensive (5–6 days/week), short duration (2 weeks) physical activity interventions improve markers of multidimensional health, in very frail individuals?	Analysis of the secondary dependent variables within the study (primary dependant variables of the future clinical trial). Analysis of uptake and adherence rates. Analysis of the level of satisfaction with the interventions through questionnaires with participants post-intervention.

*Participants within the feasibility study will not be recruited as participants within the proposed future clinical trial in order to protect the scientific validity of the proposed future clinical trial, as the participants within the feasibility study will already have undergone the interventions, or similar interventions. However, participants within the feasibility study will likely not still be residents on the ward, as the average stay for participants on the ward is ~3.5 weeks. As such once the proposed future clinical trial has commenced, all participants within the feasibility trial will likely have left the ward well in advance.

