### Eligibility

This study is open to both men and woman whom meet the following eligibility criteria: inpatient on the Harborne ward of the Queen Elizabeth hospital Birmingham, [name], UK; ≥65 years of age; frail according to the Fried Frailty Phenotype criteria^2^; ability to speak and read in English; not currently taking part in any other clinical trial which could potentially impact on or influence the findings of this study; not currently terminally ill with life expectancy less than the duration of the study; no severe sensory impairment which would profoundly impact on ability to undergo the intervention, even once appropriate adaptations have been made; anticipated by their care team to remain on the ward for ~21 days post-enrolment into the study.

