### Dependent variables

#### Primary dependent variables

The primary dependent variables will relate to the eight primary areas of focus of feasibility studies^22^ (utilised to establish the feasibility of a proposed future clinical trial within this setting), relating to: acceptability, demand, implementation, practicality, adaptation, integration, expansion and limited-efficacy testing.

These dependent variables will be assessed through semi-structured interviews with study participants and focus groups with ward staff post-intervention. Participant uptake and adherence records will also be employed throughout. These methods seek to attain answers to the following questions and parameters relating to the eight primary areas of enquiry for this feasibility study outlined in further detail in table 1.

In order to enhance trustworthiness in the qualitative component of this research, several methods will be employed:

The researcher gathering the data will keep a reflective journal in which they will record information about themselves, their activities and the methods used. Field notes will include time, date and location, participant’s actual notes, and the researcher’s own questions and comments. This will lend to logging and documenting what is learnt about the study, the intervention, the setting, the participants, and used to refine focus for future interviews through assessing the following questions: What is important? What is it I need to find out more about? What would I want to focus on more closely if I could do the interview again, or in future interviews?^31^

Data will be gathered from study participants and ward staff in order to collect data from multiple sources (triangulate information). This study will also employ more than one researcher to analyse the qualitative data in order to enhance triangulation and validity.

Enough details will be given about the participants and the setting to make decisions about the quality of the findings from the qualitative analysis. Detailed descriptions about the participants experiences and the setting will be provided by the researcher.

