### Data collection

Data will predominantly be collected at two main time points: baseline and post-intervention (table 2).

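### The safety section merges stopping the exercise sessions with leaving the study, so participants not cleared to exercise after an adverse event may give no post-intervention data

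*Protocol article*

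**What the plan says.** **After an adverse event.** Under Safety reporting and monitoring, the participant is referred to the clinical care team, and the research team is "to recommend that the participant withdraw from the study unless they have been cleared to continue exercise by their attending physician". This is a recommendation, and it does not apply to anyone whom the physician has cleared.

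**When data are collected.** The Data collection section states: "Data will predominantly be collected at two main time points: baseline and post-intervention". For the feasibility outcomes, the section Primary dependent variables states: "These dependent variables will be assessed through semi-structured interviews with study participants and focus groups with ward staff post-intervention". It adds: "Participant uptake and adherence records will also be employed throughout". Retention is also recorded during the study and enters the final feasibility analysis (Post-intervention assessment; Statistical methods).

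**The assessment window.** The section Post-intervention assessment states: "Primary and secondary dependent variables will be assessed between 1 and 5 days post-intervention cessation". Table 2 puts the last session on Sunday of week 2 and assessments on Monday to Saturday of week 3.

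**Expected stay.** Eligibility requires that the patient be "anticipated by their care team to remain on the ward for ~21 days post-enrolment into the study". The footnote to Table 1 says that "the average stay for participants on the ward is ~3.5 weeks". Patients about to be discharged are not given an information sheet (Identification).

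**The concern.** Stopping treatment and leaving a study are different events, and a protocol normally keeps them apart so that people who stop treatment can still be measured. Here the criterion concerns exercise and the recommended action concerns the study. A participant who takes the advice has left before the only point at which interviews, satisfaction questionnaires and repeat outcome measurements are described.

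These are the people a feasibility study most needs to hear from. Retention counts show how many left. A participant's own account of what went wrong, and of what would have to be adapted, comes from the interview. The target of about 30 participants is justified only by expected saturation in the qualitative component, so each lost interview also weakens the stated basis for the sample size.

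**Working it through.** **Step 1. Which outcomes depend on the participant still being in the study?** From Table 1 and the sections on dependent variables:

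- Adaptation: participant interviews only. Exposed.
- Acceptability: uptake analysis, participant interviews and staff focus groups. The interview part is exposed.
- Implementation and Practicality: participant interviews and staff focus groups. The interview part is exposed.
- Limited-efficacy testing: secondary variables, uptake and adherence, and post-intervention satisfaction questionnaires. The secondary variables and questionnaires are exposed.
- Demand and Integration: uptake and adherence records and staff focus groups. Not exposed.
- Expansion: interviews or a focus group with staff. Not exposed.

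Adverse events are monitored at each testing or exercise session, so someone who has left has neither of those contact points. Local hospital procedures are also to be followed and may cover this.

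**Step 2. How large could the effect be?** Let f be the fraction without post-intervention data, m_s the true mean change in those who stay and m_l that in those who leave. The mean over everyone is (1 − f)·m_s + f·m_l, so

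mean in stayers − mean in everyone = f·(m_s − m_l).

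The documents give neither f nor the difference. Both are assumptions here, with leavers assumed to do worse and f covering loss for any reason:

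| Assumed f | With data, of 30 | Shift if difference is 0.5 SD | Shift if difference is 1 SD |
|---|---|---|---|
| 10% | 27 | 0.05 SD | 0.10 SD |
| 20% | 24 | 0.10 SD | 0.20 SD |
| 30% | 21 | 0.15 SD | 0.30 SD |
| 40% | 18 | 0.20 SD | 0.40 SD |

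**Step 3. Does the calendar leave room for assessment before discharge?** Take Monday of week 0 as day 0. In Table 2, enrolment is on days 2 to 5 (Wednesday to Saturday) and assessment on days 21 to 26 (Monday to Saturday of week 3).

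- Shortest interval: 21 − 5 = 16 days. Longest: 26 − 2 = 24 days.
- Monday of week 3 falls 21 − 5 = 16 to 21 − 2 = 19 days after enrolment, so it is within 21 days for every enrolment day.
- Combinations beyond 21 days: Wednesday enrolment with Thursday, Friday or Saturday assessment (3), Thursday with Friday or Saturday (2), Friday with Saturday (1). That is 6 of 4 × 6 = 24.

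The expected-stay criterion therefore fits the schedule if assessment is booked early enough in week 3. A patient enrolled on Wednesday who stays exactly 21 days has Monday to Wednesday available.

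**Step 4. Do the text and Table 2 agree on the window?** The last session is on day 20 (Sunday of week 2). Assessments on days 21 to 26 come 1 to 6 days later, but the text says 1 to 5. The baseline window shows that the text counts days in the same way: sessions start on day 7, so baseline days 2 to 5 are 5 to 2 days before, exactly as the section Baseline assessment states. The post-intervention mismatch is therefore real, and it is one day.

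**The case against.** The strongest case on the other side is that the clause is a recommendation with an exception, in a condensed article whose full protocol may describe withdrawal procedures. Several stronger readings are tempting, and the documents do not support them.

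- **Everyone with an adverse event is told to leave.** Not so. Those cleared by the attending physician are outside the clause, and the others are advised, not removed.
- **The analysis is of completers only.** A reader might infer this, but it is nowhere stated. The window is counted from the end of the intervention, which can be read as a participant's own stopping date, so someone who stops early and stays in the study could be assessed. That reading does not help a person who has followed advice to leave the study.
- **Adherence and all acceptability data are biased.** Uptake, adherence and retention are recorded throughout, and staff can report why patients stopped.
- **The expected-stay criterion contradicts Table 2.** It does not. The criterion is approximate, and all 6 late combinations can be avoided by scheduling. The average stay of 3.5 weeks (24.5 days) describes the whole ward stay, whereas eligibility selects on expected stay after enrolment.
- **The bias has been quantified.** It has not. The shifts in the table are conditional on assumed figures, and the protocol already says the efficacy results are unpowered and need caution.

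A further objection has force. The secondary variables include leg strength and power and a physical performance battery. Whether someone not cleared to exercise may do such tests is a clinical decision, and a statistical request to keep people in the study must not pre-empt it. The absence of a discharge visit or a missing-data rule from the article is not counted as an error here.

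What remains is the clause itself. It is a stated rule, not a gap, and it attaches the wrong consequence to its own test.

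**Conclusion.** The point holds in a limited form and is worth changing. The safety section ties leaving the study to not being cleared for exercise. Those who act on that would tend to be missing from the interviews, the satisfaction questionnaires and the post-intervention measurements. Adaptation is the most exposed area because Table 1 gives it no other source; acceptability and pre-post change are affected in part.

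The likely direction favours the interventions, on the assumption that people who leave after an adverse event did worse or found the programme harder. The size is unknown. The shift of 0.05 to 0.20 SD in mean change (0.5 SD difference, 10% to 40% loss) shows scale only, and this clause would account for only part of any such loss.

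The one-day disagreement over the assessment window is certain but minor, and it has no bearing on the bias argument.

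**What to change.** 1. Leave the clinical rule on continuing exercise unchanged. In Safety reporting and monitoring, separate stopping the sessions from withdrawing from the study. Unless consent is withdrawn (or, for participants without capacity, the consultee advises withdrawal), the participant stays in for the interview, the questionnaires, safety follow-up and those assessments that the clinical team considers suitable.
2. Where discharge before week 3 is foreseen, offer the interview and feasible assessments before the patient leaves, keeping the existing 24-hour gap after the last session. Record the number of sessions done and the days since the last one.
3. Book assessments early in week 3 for patients whose expected stay of about 21 days ends before Saturday.
4. Reconcile the post-intervention window between the text (1 to 5 days) and Table 2 (1 to 6 days).

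The cost is protocol wording, two extra recorded items and some assessments done earlier than planned. The downside is less uniform timing and exposure: some post-intervention values will follow fewer than 10 sessions. The recorded items let this be shown and allowed for in the interpretation.
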